### 6.1. Plans to Give Access to the Full Protocol and Participant Level-Data

Access to the full protocol and participant-level data upon reasonable request to the corresponding author.

### 6.2. Patient and Public Involvement

Patients would be involved in the design, conduct, reporting, or dissemination plans of this research. Refer to the Methods section for additional details.

### 6.3. Dissemination Plans

The results of primary and secondary outcomes of this clinical trial will be available to the scientific community in a peer-reviewed journal devoted to the topic of interest.

### 6.4. Composition of the Data Monitoring Committee, Its Role, and Reporting Structure

As this trial involves minimal risks to the patients, no data monitoring committee will be established.

### 6.5. Adverse Event Reporting

The risks related to YBM intervention are minimal. Consequently, adverse events are not expected.

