### 2.3. Participants

The target population corresponds to people aged 60 years and more with any type of MCI, and the eligibility criteria for the selection of the sample consisted of the following:Having 60 years and above,People who have MCI are diagnosed by three criteria:
➢by a neurologist and/or psychiatrist, and/or geriatrician, and/or neuropsychologist. through evaluation by saying that they had memory problems confirmed by an informant (in case they have a formal or informal caregiver or simply, their partner), (but without problems in their activities of daily living);➢and with a score < 21 on the Montreal Cognitive Assessment (MoCA < 21).
Without dementia, according to the criteria of the Clinical Dementia Rating Scale (CDR), a score of 0.05.

The Exclusion criteria would be:People who performed yoga and/or mindfulness within the last 6 monthsThe presence of a psychiatric clinical diagnosis; or neurological/cerebrovascular condition.Presence of a disabling physical illness or/and presence of a disability that limits and/or impede communication, such as major impairments in eyesight, and/ hearing or upper limb motor movements, and/or other health problem that would interfere with regular yoga and mindfulness practice.

Attendants to the secondary care center (clinical hospital Universidad de Chile) who meet these criteria will be invited to participate in the study and will be randomized to an experiment or control group.

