## 3. Intervention Program

The Yoga based mindfulness intervention (YBM) will be based on video recording according to the following characteristics: (a) information about yoga and mindfulness will be delivered to seniors through specific exercises in each session (b) The mindful chair-based Hatha yoga will be used with an emphasis on proper Hatha yoga physical exercise or body awareness exercises [60,61] and mindfulness. If they find themselves unable to do a particular posture, they should be free to skip it and engage with their bodies with the attitude of kindness and acceptance, and after the completion of each posture, the participants will be asked to be mindful of muscles they will be tensing, stretching and which one will be used to keep their body balanced; (c) The mindfulness component will be based on (MBSR) guideline developed by Kabat-Zinn [48] which has been adapted from mindfulness protocol developed by Wong [32] for older people with MCI. The program will include both formal and informal practices. Participants will be taught to practice formal mindfulness techniques such as “body scan”, and “breath” meditations to observe and maintain attention on an object of meditation without judgment and reactivity even when one becomes distracted by drifting thoughts or unpleasant emotions and ‘loving-kindness’ meditation to cultivate kindness towards all beings, including oneself [32]. The informal practice involves spreading awareness to daily experiences such as mindful walking and eating [32]. The informal practice will also include mental exercises such as reading and solving puzzles, as well as being aware of daily interactions and other ADLs.

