### 3.1. Procedures

Participants who would be assigned to the experimental group will receive the Yoga-based mindfulness intervention (YBM) for an hour, once weekly, for a total of 8 weeks. The YBM intervention program has been adapted to the needs, goals, and levels of understanding of MCI patients and will be executed based on a video that has been recorded by facilitators who have knowledge about yoga ([name]) and mindfulness ([name]) and who are different from those who will act as outcomes assessor and will be sent to the program attendees through WhatsApp application in order to watch and listen to on personal phones, computers or tablets. The control group will receive a passive psychoeducation with general information about wellness, self-care in health, and the promotion of exercise that will be delivered via text through the WhatsApp application each week.

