### 3.2. Criteria for Stopping or Modifying Allocated Interventions

The neurologist who is in contact with patients for their treatment will be informed If patients allocated to the intervention or to the comparator present worsening of their physical or cognitive function at some point in the trial. Interventions will likewise be interrupted if a patient requests to withdraw from the study. Accordingly, this information will be informed to the affected participant and the Scientific Ethics Committee of the Clinical Hospital of the Universidad de Chile.

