### 3.3. Plans to Improve Adherence to Intervention Protocols

Adherence to trial protocols will be ensured through participants’ satisfaction with the program. Therefore, they will be given telephone calls in order to keep a record of each session with the patients, and in case they have a doubt regarding the intervention program and contents. Moreover, the intervention program will be explained to their caregivers, and they will also be contacted in order to have their feedback about the intervention program.

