## 8. Conclusions

The YBM intervention protocol based on video recording has been adapted and designed. It is expected to be implemented as an acceptable and effective non-pharmacological option for older people with MCI. Providing evidence-based programs as a possible preventive treatment strategy for Alzheimer’s disease in the elderly has relevant implications for public mental health services in Chile.

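### Section 6.5 puts an expectation of no adverse events in place of a plan to collect and report them, so the trial will produce no systematic harms data

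*Protocol article*

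**What the plan says.** All from the protocol article:

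- **Section 6.5, Adverse Event Reporting**, consists only of this: "The risks related to YBM intervention are minimal. Consequently, adverse events are not expected".
- **Section 6.4** uses the same premise: "As this trial involves minimal risks to the patients, no data monitoring committee will be established".
- **Section 3.2** has one safety route, for both arms. The neurologist "will be informed If patients allocated to the intervention or to the comparator present worsening of their physical or cognitive function". It also provides for informing the affected participant and the ethics committee.
- **Section 3.3** describes contact during the programme: "they will be given telephone calls in order to keep a record of each session with the patients". Its stated purposes are adherence and answering doubts. Caregivers are contacted for feedback on the programme.
- **Content, delivery and population.** Section 3: "The mindful chair-based Hatha yoga will be used with an emphasis on proper Hatha yoga physical exercise or body awareness exercises". Section 3.1: the video "will be sent to the program attendees through WhatsApp application in order to watch and listen to on personal phones, computers or tablets". Section 2.3: "The target population corresponds to people aged 60 years and more with any type of MCI".
- **Outcomes and reporting.** Section 4 and Table 1 list MoCA, Barthel, IADL, PHI, GAI and GDS-5. Section 6.3 promises the primary and secondary outcomes. Under section 5.1, people who withdraw are not assessed again.
- **Section 8**: "It is expected to be implemented as an acceptable and effective non-pharmacological option for older people with MCI".

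**The concern.** A section on adverse event reporting should say what will be asked, of whom and when, and how it will be reported. This one predicts the result instead. An expectation that events will be rare may be reasonable, but it does not replace looking for them.

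The prediction also fits poorly with the article's own account of the population. The Background and Discussion link frailty to cognitive impairment and describe frail older people as at higher risk of functional decline and hospitalization. Section 2.3 excludes people whose health would interfere with the practice, which concedes some physical demand.

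If events are recorded only when a participant happens to mention them, the final report cannot give harm counts that are comparable between arms. Section 7 foresees a larger study and relevance to national policy if the intervention works, and readers at that stage will want those counts. Someone who stops because of a fall or pain would leave the data with no reason recorded.

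**Working it through.** **Step 1: does anything else in the article do the work of section 6.5?** A systematic harms record needs an event definition, a question put to everyone in both arms, and a report by arm.

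| Place | What it gives | What it lacks |
|---|---|---|
| 3.2 | Notification of worsening, both arms | How worsening is detected. A fall, pain or dizziness need not count as worsening. No report by arm |
| 3.3 | Calls recording each session; caregiver contact | Any question about harm. Whether the control arm, which receives weekly texts (3.1), is called on the same schedule. Who makes the calls |
| 4 and Table 1 | Function, mood, well-being and cognition at post-test, 3 and 6 months, both arms | Discrete events. Group means can hide a few injured people |
| 5.1 | Calls if participants have doubts | Any assessment, or reason recorded, after withdrawal |
| 6.3 | Publication of primary and secondary outcomes | Harms |
| 6.4 | No data monitoring committee | (A choice, not an error; it does not fill the gap) |

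No row, and no combination of rows, supplies all three elements.

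**Step 2: what could the trial show about harms if events were asked for?** The article gives no harms figure, so there is none to reproduce. The only input is the number exposed: 22 allocated to YBM, and 18 if the planned 20% drop-out occurs (both from section 2.6).

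With zero events in n people, the exact upper limit solves (1 − p)^n = α, so p = 1 − α^(1/n).

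- n = 22, one-sided 95%: 1 − 0.05^(1/22) = 12.7%
- n = 22, two-sided 95%: 1 − 0.025^(1/22) = 15.4%
- n = 18, one-sided 95%: 1 − 0.05^(1/18) = 15.3%
- n = 18, two-sided 95%: 1 − 0.025^(1/18) = 18.5%

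**Step 3: how likely is at least one event among 22?** The article states no event rate, so the rates below are assumptions. The formula is 1 − (1 − p)^22.

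| Assumed risk per participant | Chance of at least one event |
|---|---|
| 1% | 20% |
| 2% | 36% |
| 5% | 68% |
| 10% | 90% |

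At a risk of a few per cent, seeing at least one event is a realistic prospect. At 1%, it is more likely than not that none occurs. These figures describe what 22 people can show under good collection. They do not measure the damage done by section 6.5, which is that the counts would not be collected systematically at all.

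**The case against.** The case for the plan has substance.

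- **The risk is mitigated by design.** The yoga is chair-based, participants may skip any posture they cannot manage, people with disabling illness or disability are excluded, and caregivers have the programme explained to them. The Background cites earlier work describing yoga as safe in this population. Calling the risk minimal is defensible. This stands, but low risk is not a reason to leave events unrecorded.
- **Some safety information exists.** A reader might infer that the trial will have no safety data whatever. The documents do not support that: there is the worsening notification, the session calls, and repeated function and mood scales in both arms. What is missing is systematic harms data.
- **Supervision.** A reader might picture participants practising alone and unwatched at home. The article says only that videos go to personal devices and mentions no live instructor. Absence of supervision is an inference, and caregiver contact is described.
- **Acceptability.** Section 8 might be read as a safety claim that the trial must support. It states an expectation, and no objective or hypothesis concerns safety.
- **Unequal reporting.** A reader might conclude that events will be volunteered more in the YBM arm. That could happen if only that arm is called, but section 3.3 speaks of participants generally and does not settle it.
- **Condensation.** Forms and event definitions are often left to the full protocol. That would excuse a section that deferred the detail. Section 6.5 does not defer; it draws a conclusion from the premise of minimal risk.

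**Conclusion.** The point holds in this form: section 6.5 sets out no collection or reporting of adverse events. Apart from a worsening notification whose means of detection is not stated, the article plans no systematic harms data for a physical programme delivered by recorded video to people aged 60 and over with MCI.

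It should be corrected, because correction is cheap and counts not collected during the trial cannot be reliably recovered afterwards. It does not touch the primary MoCA comparison. Nor does it show that the programme is unsafe, or that doing without a monitoring committee is wrong in a trial of 44.

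Even after correction the evidence would be descriptive. Zero events among 22 would leave a risk of up to 12.7% (one-sided) or 15.4% (two-sided) compatible with the data. Those limits assume that all 22 are asked, that events are independent between participants, and that each participant is counted once.

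**What to change.** Replace the sentence in section 6.5 with a statement to this effect: a short fixed set of harm questions (falls, injury, pain, dizziness, unplanned care) will be asked in the same words and on the same schedule in both arms, on the telephone calls already planned in section 3.3. The callers, not the blinded outcome assessors, will ask them, so that talk about practice does not reveal the allocation. The reason for any withdrawal will be recorded at the last contact. The number of participants with each event, and the number of events, will be reported descriptively by arm without significance tests.

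Reconcile sections 3.2, 3.3 and 6.5: say how worsening under 3.2 comes to notice, state in 3.3 that both arms are called and by whom, and refer to both from 6.5. Add harms to Table 1 and to section 6.3. What should be done clinically after an event is for the investigators and the ethics committee, and is not addressed here.

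**Cost:** slightly longer calls, one form and one extra table. If the control arm is not currently due to be called for each session, those calls are an added workload. They also give both arms equal telephone contact.

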### 6.6. Strategies for Communicating Important Protocol Amendments

Any modifications to the trial protocol which may affect the safety of the participants must be approved by the Scientific Ethics Committee of the Clinical Hospital of the Universidad de Chile.

## 7. Discussion

With the aging of the global population aging, cognitive impairment (CI), including dementia and mild cognitive impairment (MCI), has become an important issue in public health [78,79]. The prodromal stage of dementia is also referred to as mild cognitive impairment (MCI) [80], which is characterized by a measurable decline of cognition without losing the capacity to perform the activities of daily life. In addition, MCI patients often manifest symptoms such as depression, anxiety, apathy, and irritability [81], which increases the likelihood of progressing to dementia [82]. Moreover, frailty is a multidimensional condition typical of elders, which are strongly associated with cognitive impairment [83]. Recent evidence revealed a significant correlation between physical and cognitive decline in the elderly with frailty [84]. Frail senior citizens have a higher risk of functional decline, hospitalization, and mortality [84].

Current pharmacological treatment options for MCI are limited [13], emphasizing the need for effective non-pharmacological treatments. Mindfulness-based interventions have shown a promising effect on several health factors related to the increased risk of progression from MCI to dementia, for instance, depression, stress, cognitive decline, as well as change in brain structure and immune system [32,51,56].

The present study would be the first randomized controlled trial aimed at evaluating the effectiveness of yoga-based mindfulness (YBM) intervention versus psycho-educational sessions in improving cognitive and physical functions and mental health outcomes for older adults with mild cognitive impairment (MCI) in Chile.

The intervention has been adopted. There is fresh evidence of the effectiveness of mind-body interventions, including yoga and mindfulness, in older adults with MCI. Currently, there is no local evidence of any psychosocial intervention based on mind-body therapy focused on older people with MCI. In Chile, adults over 60 will increase from the current 15.7% of the population to 32.9% by 2050 [5]. Therefore, aging is a highly relevant issue for the social and public health systems, especially in Chile, a country with great social and health inequalities [24].

It is important that Chile start collecting scientific evidence on the mental health of older people and on feasible and effective interventions for this population. In the case of cognitive impairment, the evidence is not robust and seems to reaffirm the need for early interventions. Present investigation can be an important contribution to the knowledge of older adults with MCI, who are at risk of conversion to AD. If the intervention proves to be effective, it would be of great interest and would enable its replication in a larger study, which would be relevant to national public health policy. The follow-up evaluations would enable researchers to evaluate its efficacy and to study its effects in greater depth. It is important to note that the aging process requires that society be able to fulfill the needs of the elderly Chilean people in terms of public policies, programs, and resources specifically designed for this population that contribute to active aging [85]. The results could help future researchers evaluate the potential of the intervention program to be part of an international strategy aimed at strengthening the cognitive and physical function as well as the mental health of older people with MCI in Latin America.

## 8. Conclusions

The YBM intervention protocol based on video recording has been adapted and designed. It is expected to be implemented as an acceptable and effective non-pharmacological option for older people with MCI. Providing evidence-based programs as a possible preventive treatment strategy for Alzheimer’s disease in the elderly has relevant implications for public mental health services in Chile.

## Figures and Tables

**Figure 1 ijerph-19-15374-f001:**
[figure not shown]
Participant flow through the study.

**Table 1 ijerph-19-15374-t001:** Participants Timeline.

	Study Period						
	Enrolment	Allocation	Post-Allocation				Close-Out
Timepoint **	−t_1_	0	t_1_	t_2_	t_3_	t_4_	t_5_
Enrolment			Baseline	Intervention	Post	3M	6M
Eligibility screen	X						
Informed consent	X						
Allocation		X					
Intervention							
YBM Intervention				X			
Control							
PES				X			
Assessments							
MoCA	X				X	X	X
Demographic	X						
BI			X		X	X	X
IADL			X		X	X	X
PHI			X		X	X	X
GAI			X		X	X	X
GDS-5			X		X	X	X

Time points are: t_1_ baseline, t_2_ intervention period, t_3_ post-line evaluation, t_4_ 3 months follow up, t^5^ 6 months follow up; ** Montreal Cognitive Assessment (MoCA), Barthel Index (BI), Lawton Instrumental Activities of Daily Living Scale (IADL), Pemberton happiness index (PHI), Geriatric Anxiety Inventory (GAI), Geriatric Depression Scale (GDS-5).

## Data Availability

The datasets used and/or analyzed during the current study will be available from the corresponding author upon reasonable request.

## Abbreviations

MCI: Mild cognitive impairment; CI: Cognitive Impairment; AD: Alzheimer’s; MoCA: Montreal Cognitive Assessment; FDA: Food and Drug Administration; MET: Memory Enhancement Training; YBM: Yoga based- mindfulness; MBI: Mindfulness-based Intervention; MBSR: Mindfulness-based Stress Reduction; DMN: Default mode Network; PES: Psycho-educational Sessions; IADL: Instrumental Activities of Daily Living Scale; GAI: Geriatric Anxiety Inventory; GDS: Geriatric Depression Scale; BI: Barthel Index; MCID/MCIC: Minimal Clinically Important Difference or Change; PHI: Pemberton happiness index.
